## Abstract

**Background:**

Burnout syndrome is an important health problem that affects many professionals and must be addressed globally, with both organizational measures and personal interventions. Burnout of health professionals can be prevented in order to avoid personal, familial, and social consequences, as well as repercussions for patients.

**Methods/design:**

This work describes a protocol for a controlled, pragmatic, randomized clinical trial in 2 parallel groups: intervention and control. All health professionals from 7 health care centers will form the intervention group, and all health professionals from 7 different health care centers will form the control group. The intervention group will receive 16 hours of training at their work place. The Maslach's burnout inventory, the Cuestionario de Desgaste Profesional Médico or the Cuestionario de Desgaste Profesional de Enfermería, and the 28-item Goldberg's General Health Questionnaire, validated for our setting, will be used as measurement tools. Change in the average scores from the Maslach's burnout inventory emotional exhaustion scale will be compared between the intervention and control groups, measured as intention-to-treat, and the intervention will be considered effective if a minimum decrease of 20% is achieved.

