### Sample size and sampling

The main outcome variable will be the score on the emotional exhaustion sub-scale of the MBI.

In a previous study performed by this group in the same setting, the average score on this sub-scale was 24, with a standard deviation of 12 points. A change of at least 5 points with respect to the baseline (~20% of the initial value) will be considered significant. These figures do not differ from those found in other populations.

The sample is calculated as non-finite size data, using the formula proposed by Snedecor and Cochran [18].

It is therefore necessary to include ~90 subjects per group, considering a type I error <0.05 and a type II error of 20% (statistical power 80%).

However, we are going to study clusters (health centers) where the variability of the studied parameter will be lower among subjects from the same group and higher among subjects from different groups. This effect, termed the “design effect”, multiplies the needed sample size by a factor ranging from 1.5 to 5. The magnitude of this factor depends on the relationship between the intragroup and intergroup variance, termed the intraclass correlation coefficient [19]. In this case, since there are environmental factors that favor the appearance of burnout, at least moderate intraclass clustering is expected, for which we estimate the design factor will be ~2. Thus, we will need at least 180 subjects per group. If we have a loss to follow-up of ~10%, the studied population will have to be ~200 subjects per group.

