#### Analytical statistics

Initial comparability between the intervention and control groups will be analyzed with the Student's t-test in the case of independent data of quantitative variables (age, years of experience, workload, scores from the questionnaires, etc.) that fit a normal distribution, with the Mann-Whitney U non-parametric test for those not fitting a normal distribution, and with contingency tables in the case of qualitative variables (sex, marital status, professional group, type of contract, etc.).

Univariate correlations between socio-demographic and work characteristics of subjects and their score in the MBI at the beginning of the trial, as well as the correlation between the mentioned characteristics and the change observed during the follow-up, will be analyzed by use of simple linear regression models.

The correlation between the changes associated with burnout syndrome and changes in work-life quality and anxiety, as perceived by health professionals, will be measured using the correlation coefficients for score changes from the MBI, the professional quality of life questionnaire (QPL-35), and Goldberg's GHQ. Pearson's r will be used in the case of normal distributions, and Spearman's rho for non-normal distributions.

Explanatory models will be built to identify work and occupational characteristics related to work satisfaction and burnout. The dependent variable will be the score obtained from the relevant questionnaires at baseline, and the independent variables those considered as relevant in previous theoretical models or proven significant in the univariate analysis.

A comparison of average scores on the MBI will be performed between the intervention and control groups after the intervention and at the end of the follow-up in order to measure the effectiveness of the intervention, and the Student's t-test will be employed for independent data. Confidence intervals of 95% will be calculated for the differences. If the application criteria are not met for that analysis, non-parametric tests will be used (Mann-Whitney U test).

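### The 20% success rule is undefined, and the stated 80% power does not belong to it if it is used as a pass mark

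*Protocol article*

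**What the plan says.** The protocol article addresses success in four places.

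- **Abstract, Methods/design.** Change in mean emotional exhaustion (EE) on the Maslach inventory "will be compared between the intervention and control groups, measured as intention-to-treat". The same sentence then adds that "the intervention will be considered effective if a minimum decrease of 20% is achieved".
- **Sample size and sampling.** From the group's previous study, "the average score on this sub-scale was 24, with a standard deviation of 12 points". Then: "A change of at least 5 points with respect to the baseline (~20% of the initial value) will be considered significant". With a 5% type I error and 80% power, "It is therefore necessary to include ~90 subjects per group". For clustering, "we estimate the design factor will be ~2. Thus, we will need at least 180 subjects per group". Allowing for about 10% loss gives about 200 per group.
- **Dependent variable.** The outcome is the before-to-after change in EE, for each subject and for the whole sample.
- **Analytical statistics.** Mean scores are compared by t-test with 95% confidence intervals "between the intervention and control groups after the intervention and at the end of the follow-up in order to measure the effectiveness" of the intervention. GEE models that allow for health centre also address the principal objective. The 20% figure is not mentioned here.

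**The concern.** A reader cannot tell from these passages what result would count as success. The abstract gives a numerical threshold, the sample size section refers that threshold to baseline and calls it significant, and the analysis section relies on a between-group test without the threshold. No passage says which governs if they disagree.

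The choice matters because the power was calculated for only one of these rules. A threshold equal to the planning difference is much harder to meet than a test against zero. A threshold on change within the intervention arm would not use the control group at all. The headline conclusion could therefore differ from the result of the controlled comparison, and the rule could be settled after the data are seen.

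**Working it through.** **Inputs, all from Sample size and sampling:** difference 5 points; SD 12; baseline mean 24; type I error 0.05; power 80%; design factor 2; 180 analysed per group. Exactly 20% of 24 is 4.8 points. Sidedness is not stated.

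**1. Reproduce the plan's sample size.** For a two-sided, two-sample comparison of means:

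n = 2 × [12 × (1.960 + 0.842) / 5]² = 90.4 per group, against about 90 stated.

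A one-sided test would need 72 and does not match. Then 90 × 2 = 180, and 180 / 0.9 = 200. The size is therefore that of a two-sided test of a between-group difference from zero.

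**2. Power of that test.**

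- SE of the difference = 12 × √(2 × 2 / 180) = 1.79.
- Smallest significant observed difference = 1.96 × 1.79 = 3.5 points (about 3.9 with a t distribution on 12 degrees of freedom, from 14 centres).
- Power at a true 5 points = Φ((5 − 3.51) / 1.79) = 79.8%, which agrees with the stated 80%.

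**3. The 20% as a pass mark on the observed between-group difference.** P(pass) = Φ((true − mark) / SE).

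| True difference | Mark 5 points | Mark 4.8 points |
|---|---|---|
| 0 | 0.3% | 0.4% |
| 4 | 29% | 33% |
| 5 | 50% | 54% |
| 6 | 71% | 75% |

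With the mark at 5 and a true difference of 5, the result is Φ(0) = 50% at any sample size. With 200 analysed per group the test's power rises to 83.8%, but this figure stays at 50%. An 80% chance of passing a 5-point mark needs a true difference of 5 + 0.842 × 1.79 = 6.5 points.

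Requiring both significance and 5 points does not change this. Both marks lie above the significance boundary of 3.5 (or 3.9) points at the planned SE, so the 20% is the binding condition.

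**4. The 20% as a fall from baseline in the intervention arm.** The SD of change is not given, so 8 and 12 are assumed. Suppose both arms fall by 5 points and the intervention has no effect.

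- SE of the arm mean = SD × √(2 / 180) = 0.84 (SD 8) or 1.26 (SD 12).
- P(fall ≥ 5) = 50% for either SD.
- P(fall ≥ 4.8) = Φ(0.2 / 0.84) = 59% (SD 8) or Φ(0.2 / 1.26) = 56% (SD 12).

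**The case against.** The strongest defence is that the abstract's 20% clause completes a sentence that already names a between-group, intention-to-treat comparison. The abstract itself does not refer to baseline; that wording is only in the sample size section. There the 5 points serve as the difference in a two-sample calculation, so calling such a change significant may be loose wording for the smallest relevant difference. Asking for a minimum effect in addition to significance is also a legitimate choice.

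Much of this stands. A reader might infer that the trial will declare success on a before-after fall and ignore its controls. The documents do not support that as the stated rule, because the abstract, the t-test and the GEE models all compare groups. It remains a possible reading only because the sample size section says baseline and nothing resolves it.

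The two harms also cannot apply together. On the between-group reading the mark is stricter than the test, with a false-positive probability of about 0.3%, and equal falls in both arms would generally fail. On the within-arm reading equal falls could pass.

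A reader might further infer an inflated type I error from testing after the intervention and again at the end of follow-up. That would require success at either time point to suffice, which no passage states, and the ranking of time points may be left to an analysis plan that is not shown. It is not part of this point.

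The defence does not remove the mismatch. On the reading most favourable to the authors, a between-group pass mark is met about half the time under the planned effect, against the stated 80%.

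**Conclusion.** The concern holds in this form: the success criterion is not defined, and the stated power belongs to a different rule if the 20% is a pass mark.

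- **Between-group pass mark.** The chance of success at a true 5-point difference is 50% (54% at 4.8 points), not 80%. Observed differences of about 3.5 to 5 points would be significant yet not effective.
- **Fall in the intervention arm.** The control arm plays no part in the decision, and a 5-point fall common to both arms would pass about 50–59% of the time.
- **Aid to interpretation only.** The 80% power stands and only the wording is at fault.

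The 50% figure needs no assumption beyond a true difference equal to the mark and a symmetric estimate. The 54% figure uses SD 12, which the article gives for the score, and a baseline mean of 24. The within-arm figures rest on an assumed SD of change (8 to 12) and a hypothetical common fall. The documents do not establish which reading was intended.

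**What to change.** - **Criterion.** State one rule: the intervention is effective if the cluster-adjusted between-group difference in EE favours intervention and its 95% confidence interval excludes zero.
- **Sample size and sampling.** Describe the 5 points as a difference between groups instead of a change relative to baseline, and as the planning difference instead of a definition of significance.
- **Abstract.** Say that the 20% is a between-group difference used to judge the clinical relevance of the estimate and its interval.
- **If the sponsor keeps the 20% as a pass mark.** Say that it applies to the between-group difference and how it combines with the test, and restate the power as about 50–55% at a true 5-point difference.

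The cost is rewording of the abstract and of the sample size and analysis paragraphs. The recommended rule needs no change to the data collected or the number of participants.

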**Discussion:**

Due to the deleterious consequences of burnout syndrome for people suffering from it and for the organization where they work, it is necessary to evaluate the effectiveness of certain interventions for its prevention. Organizational measures are important for preventing burnout syndrome, but so is providing professionals with coping strategies, as this group intervention intends to do.

**Trial registration:**

ClinicalTrials.gov processed this record on June 10, 2013. ClinicalTrials.gov Identifier: NCT01870154.

## Background

There is a high prevalence of job burnout or profession related wearing down, which is considered to be an adaptive disorder to chronic work stress and entails harmful consequences for the individual suffering from it and the employing organization [1].

Studies performed in primary care show that around 40% of family doctors suffer from burnout syndrome to some degree [2], although with variable results ranging from 10% to 80% [3].

Concern about the satisfaction of health professionals led to initial studies by Donabedian in 1966, and later by Freebon and Greenlick in 1973.

Donabedian states that the degree of quality of the services provided by a health care system is directly related to the satisfaction level of the professionals working within it, and reveals that their demoralization is the main difficulty faced by directors and managers of health care centers (HCCs).

Work motivation is the result of a series of interactions between individual effort, obtained output, organizational rewards, and personal objectives. Even though any worker is susceptible to dejection, those most likely to suffer from it are the ones directly in contact with the public.

The term “work stress” was first introduced by McGrath in 1970 and defined as the imbalance perceived between a demand and the individual's capacity to fulfill it under conditions where failing to fulfill that demand entails significant consequences.

Even though Donabedian and Freebon were the first ones to associate work satisfaction with the quality of supplied services, it was not until 1974 that psychoanalyst Herbert Freudenberger talks of “work disease” for the first time, defining the “burnout syndrome” as a state of exhaustion or frustration resulting from dedication to a cause, way of life, or relationship that does not result in the expected reinforcement [4].

Herbert Freudenberger mentions that this syndrome is more frequent in helping professions, where facing intense emotions of pain, disease, and/or psychological suffering is common.

Health professionals work with the most intense emotional facets of human beings (suffering, fear, sexuality, and death), and they cannot, nor must, be completely indifferent towards them. Thus, it is easy for them to be subjected to a high degree of chronic stress and a state of physical and psychological exhaustion.

Stress is the response (physiological, psychological, and behavioral) of beings when facing events, situations, people, or objects perceived as stressful, which consequently induces a stress response that is essential for survival. According to Hans Seyle, the 3 physiological phases that the response follows are: alarm, adaptation or resistance, and exhaustion. During stressful situations, attention increases and the brain focuses on the perceived challenge. When stress becomes chronic, it stops being a physiological stimulus and becomes detrimental to health [5].

In 1982, psychologist Maslach describes the responses of workers to different stressful situations in their work life, and tries to define the basic characteristics of the syndrome that she terms “burnout syndrome” [6].

The basic characteristics of the syndrome are: emotional exhaustion, feeling of fatigue with both mental (anxiety, anguish, sexual dysfunction, chronic fatigue, etc.) and physical (spastic colon, dyspepsia, headache, myalgia, etc.) manifestations, and depersonalization. Depersonalization results in isolation behaviors, insensitivity, dehumanization, negativity, distancing from patients, low personal fulfillment (dissatisfaction about professional achievements and a desire to give up). In the health setting, mental fatigue results in a state of exhaustion in the face of those task requirements that the worker feels no interest to perform; depersonalization implies a rejection behavior towards patients, referring to them as objects; and lack of personal fulfillment consists of a negative attitude towards oneself and work, loss of interest towards work, irritability, low productivity, and low self-esteem. Thus, the burnout syndrome has important family and social repercussions, as well as for the work environment and organization, which translate into absenteeism from work, decrease of worker and user satisfaction, job mobility, and loss of productivity [3,5,7].

In the health setting, there is a serious concern about the quality of the care provided to the community and user's degree of satisfaction, whereas less attention is dedicated to the work-related health of the professionals. However, it has been demonstrated that dissatisfaction of health professionals entails an important economic and social cost due to its effect on the work environment, performance, and supply of health care.

For the last decades, we are experiencing a gradual increase of health care demand as a consequence of a population that is more critical and demanding of the care provided by health professionals. Additionally, this modification of health habits in the general population has not been accompanied by the administrative and managerial strategies necessary to provide an appropriate health care work environment.

Work satisfaction has not significantly changed in the last 10 years despite the important changes introduced by the reform of the Spanish primary care system. There is evidence that some aspects related to work satisfaction (work excess, labor tension, and promotion) have worsened. These factors can be a source of stress that leads to burnout when they are permanently maintained and overcome the individual's self-defense mechanisms. Variables related to the syndrome are excessive number of patient consultations, excessive responsibility over clinical decisions that exceed the level appropriate for the primary care setting, and difficulties in accessing continuing medical training [8].

In environments that are prone to generating this disorder, a series of factors are usually observed at an organizational level: organizational bureaucratic culture with scarce actual participation in the decision-making processes that may affect the staff; performance evaluation based on quantitative aspects and limited appreciation of qualitative ones; poor organization of tasks, job assignments, and macro-social factors such as degree of complexity and difficulty, lack of supervisor and partner support, scarce encouragement for team work, unjustified lack of resources, low or no planning, few possibilities for promotion; and additional factors [9].

Training programs aimed at preventing burnout syndrome must include training at various levels. At an organizational level, training workers in organizational development and change is required. The inter-personal level takes into account working groups and social interaction, and therefore training programs on social support, social skills, self-efficacy, and leadership, among others, must be included. The individual level must provide solutions to personal needs for coping with stress [10].

Since stress is unavoidable, it is most important to educate the worker on how to deal with it as efficiently as possible [11,12]. It is estimated that around two thirds of all diseases are related to stress, and even though it is not a cause-and-effect relationship, stress is an important factor that interacts with other biological, psychological, and social variables, resulting in numerous physical and mental pathologies [13].

Stress coping techniques aim to modify any aspects of the triple response (psycho-physiological, cognitive, and behavioral) generated by the organism when facing stress [14].

Control over activation of the psycho-physiological component allows the person to cope with daily life stressors by controlling physical symptoms resulting from the generated anxiety (palpitations, dizziness, muscle tension, etc.).

Techniques on controlling the initiation of the response are easily learned strategies that do not require much training time and can be acquired at any age. They can be carried out wherever the individual is, without the need for special conditions for their application. With adequate learning, they are able to control stress and anxiety almost immediately [15].

People are the most important resource in the health care system for achieving its objectives. The burnout syndrome is considered to be an adaptive disorder to chronic work stress [1], therefore stress-interventions for health professionals will contribute to reducing it and consequently improve population care.

In a previous research project developed by our group, *Effectiveness of two interventions on primary health professionals with burnout for dealing with stress*, of which 2 partial articles have been published [16,17], it was proven that burnout is a very wide-spread problem and carrying out a trans-personal relaxation workshop improves psycho-pathologies, as measured by Goldberg's test, and emotional exhaustion, the most important component of burnout, as measured by the Maslach's burnout inventory (MBI).

From a clinical perspective, burnout can be considered a type of adaptive disorder related to psycho-social work stressors and the existence of a persistent imbalance between demands and available resources for fulfilling them, expectations and perceived results, as well as performed effort and obtained reinforcements. The pathology results from an accumulation of risk factors, whether they are personal, organizational, work-related, or other, and from the lack of protective factors and resistance to experienced stress [3].

Apart from the need for organizational measures to improve the situation, establishing interventions aimed at minimizing the prevalence of burnout syndrome may be useful. Thus, we consider this study as a continuation to the previous one, seeking an effective intervention aimed at all health professionals within a primary care team.

The novelty of this study is that the intervention will be performed on all health professionals from a primary care team, acting on both personal and inter-personal levels, which we estimate will reinforce the effect of the intervention. Some of the main variables that affect organizational behavior, and therefore the appearance of the burnout syndrome, are found in the social-interpersonal realm. This syndrome has its origin in the interpersonal professional relationships that are established within the work environment. The objective is to train workers to improve social processes (formal and informal) that are developed during their work activities [10].

